##### Work absenteeism by parents and school absenteeism by children

An adapted version of the Dutch Health and Labor Questionnaire will be used to measure work absenteeism by parents, school absenteeism by children and indirect costs of healthcare utilisation.^32^ This adapted version contains three items. Parents indicate whether their child has been absent from school due to symptoms of nausea, and if yes, the amount of hours per week. For work absenteeism by parents, parents indicate the number of hours they worked less on average because of their child’s symptoms of nausea. For the indirect costs of healthcare utilisation, parents indicate additional costs they had due to symptoms of nausea of their child over the past 4 weeks.

##### Somatisation

The Children’s Somatization Inventory (CSI) measures the extent to which children and adolescents experience somatic symptoms. The questionnaire has been shown a valid and reliable self-report instrument in the paediatric population.^33^ The CSI consists of 35 items and on a 5-point Likert scale (0=not at all to 4=a whole lot) and children rate the extent to which they experienced somatic symptoms in the previous 2 weeks. The total score is calculated by summing up the 35 items, with higher scores indicating higher intensity of somatic complaints experienced by the child.

In order to calculate a separate CSI score for non-gastrointestinal (non-GI) symptoms, seven items on GI symptoms (nausea, constipation, diarrhoea, epigastric and abdominal pain, vomiting and bloating) are left out. The total score of somatic symptoms without GI-symptoms is calculated by summing up the scores of non-GI symptoms, with higher scores reflecting higher intensity of non-GI somatic complaints.

##### Adequate relief

Parents and children will be asked whether adequate relief of symptoms of nausea has occurred, using a dichotomous scale (yes/no). Adequate relief has been previously used as an endpoint in clinical trials assessing HT in children and adolescents^20^ and has been shown a valid outcome measure for functional gastrointestinal disorders.^34^

### Sample size calculation

The primary outcome of the RCT is the proportion of patients with at least 50% reduction of their symptoms of nausea compare to baseline at 12 months follow-up. Based on our pilot study ([name] ‘A pilot-study of hypnotherapy as a treatment for functional nausea in children’) and the success percentages in studies using HT in adults with FD^35^ and in paediatric patients with cancer,^14^ we expect that 80% of the children in the HT group will have >50% reduction of their symptoms of nausea after 1 year. In the SMT group, we anticipate that 50% of the children will have >50% reduction of their symptoms of nausea after 1 year. Based on these expected proportions, 45 children per group will be needed to achieve a power of 80% with a one-sided significance level of 5%. Accounting for a 10% dropout, 100 children will be included in this study. If a child is prematurely withdrawn from the study, he/she will not be replaced; data will be analysed according to the intention to treat (ITT) analysis.

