### Randomisation, blinding and treatment allocation

After obtaining informed consent, children are randomly allocated, by the treating paediatricians, to one of the two treatment arms: HT, given by a qualified therapist, or SMT, meaning treatment by the child’s paediatrician. A computerised random-number generator will be used to randomly allocate children on a 1:1 basis with varying block sized of 2, 4 and 6. To ensure allocation concealment, central randomisation will be applied and the random allocation sequence remains concealed from paediatricians enrolling children into the study. Due to the nature of HT, it is not possible to blind the participating children and healthcare professionals involved in the treatment of the participants.

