### Statistical analysis

#### Primary outcome

Outcomes will be analysed according to the ITT analysis. For the primary outcome, the χ^2^ test will be used to compare the proportions of patients with >50% reduction of symptoms of nausea (ie, severity, incidence and frequency of nausea) after 12 months’ follow-up between the two groups (HT vs SMT). For all analysis, the significance level for statistical analysis is set at α=0.05. Multiple imputation will be applied to deal with cases of missing data.

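### The 45 children per group do not follow from the stated one-sided 5% level; they match a two-sided 5% test with continuity correction, so the primary decision threshold has two readings

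*Protocol article*

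**What the plan says.** All inputs stand in the protocol article.

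- **Response rates** (Sample size calculation): "we expect that 80% of the children in the HT group will have >50% reduction" and "In the SMT group, we anticipate that 50% of the children will have >50% reduction", both at one year.
- **Level, power and result** (same section): "45 children per group will be needed to achieve a power of 80% with a one-sided significance level of 5" per cent. An allowance of 10% for dropout takes the total to 100.
- **Allocation** (Randomisation, blinding and treatment allocation): the plan will "randomly allocate children on a 1:1 basis".
- **Primary analysis** (Statistical analysis, Primary outcome): a chi-square test compares the responder proportions at 12 months, and "For all analysis, the significance level for statistical analysis is set at α=0.05". Sidedness is not mentioned, nor is a continuity correction.

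The sample size section is thus the only place that states the direction of the test.

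**The concern.** Detecting 80% against 50% with 80% power on a one-sided 5% test should take clearly fewer than 45 per group. Either the number or the stated level is wrong.

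The trial's size is not at stake; the rule for declaring success is. A reader who takes the sample size section literally, helped by the superiority aim and the directional hypothesis, would test one-sided at 5%. A reader who takes the chi-square test at 0.05 in its usual form would test two-sided. The first rule doubles the nominal chance of wrongly claiming a benefit of HT, from 2.5% to 5%, and accepts a smaller observed difference. In an open-label trial with a child-reported outcome, that choice should be fixed before results are known.

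**Working it through.** **Inputs.** p1 = 0.80 (HT), p2 = 0.50 (SMT), difference d = 0.30, 1:1 allocation, power 80% (z = 0.8416). The critical value is 1.6449 for one-sided 5% and 1.9600 for two-sided 5%. The mean proportion is 0.65.

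**Formula (pooled variance under the null).**

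n = [z_α √(2 × 0.65 × 0.35) + z_β √(0.80 × 0.20 + 0.50 × 0.50)]² / d²

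with √0.455 = 0.6745 and √0.41 = 0.6403. The continuity-corrected size is n_cc = (n/4) × [1 + √(1 + 4/(n d))]².

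**As written, one-sided 5%.**

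- n = (1.1095 + 0.5389)² / 0.09 = 30.2, so 31 per group.
- n_cc = (30.19/4) × (1 + 1.2007)² = 36.6, so 37 per group.

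The stated 45 is not reproduced.

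**Two-sided 5%.**

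- n = (1.3221 + 0.5389)² / 0.09 = 38.5, so 39 per group.
- n_cc = (38.48/4) × (1 + 1.1604)² = 44.9, so 45 per group.

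This reproduces the stated figure.

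**Other standard methods, n per group at 80% power.**

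| Method | One-sided 5% | Two-sided 5% |
|---|---|---|
| Pooled | 31 | 39 |
| Pooled, continuity-corrected | 37 | 45 |
| Unpooled | 29 | 36 |
| Unpooled, continuity-corrected | 35 | 43 |
| Arcsine | 30 | 38 |
| Fisher exact (two-sided: 2.5% per side) | 36 | 44 |

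The largest one-sided figure is 37, eight below 45, so rounding or choice of software does not explain the gap.

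**Dropout.** 45/0.90 = 50 per group, 100 in total, as stated. Starting from 31 or 37, the same step gives 35 or 42 per group, that is 70 or 84 in total.

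**Exact binomial power at 45 per group.**

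| Test | Uncorrected | Continuity-corrected |
|---|---|---|
| One-sided 5% | 92.3% | 88.2% |
| Two-sided 5% | 86.8% | 80.7% |

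Only the two-sided corrected test has the stated 80%. (The normal approximation gives 92.1% and 86.0% for the uncorrected tests.)

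**Effect on the success threshold.** Take 45 children analysed per group and 22/45 SMT responders (49%, close to the assumed 50%). The smallest HT count that reaches significance is:

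| Test | One-sided 5% | Two-sided 5% |
|---|---|---|
| Uncorrected | 30/45 (18 points) | 32/45 (22 points) |
| Continuity-corrected | 31/45 (20 points) | 33/45 (24 points) |

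For the uncorrected test, 30/45 gives z = 1.71 (one-sided p = 0.044, two-sided p = 0.088), 31/45 gives z = 1.93 (two-sided p = 0.054) and 32/45 gives z = 2.15 (two-sided p = 0.031). Results of 30 or 31 out of 45 would be positive on one reading and negative on the other.

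**The case against.** The strongest reply accepts the arithmetic and disputes what is built on it.

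- **The analysis section never says two-sided.** This is correct. A 2×2 chi-square can be read one-sided through its signed root, and the superiority aim and directional hypothesis would fit that. The conflict with the analysis section therefore rests on the ordinary non-directional form of the test. The mismatch inside the sample size section does not depend on it.
- **45 is the two-sided figure only with a continuity correction, which the article does not mention.** Also correct: the plain two-sided figure is 39. The match shows where 45 probably came from; it does not prove intent. A one-sided intent with a wrong number cannot be ruled out.
- **The threshold depends on the correction.** The 30/45 and 32/45 cut-offs belong to the uncorrected test. Under the corrected test, 32/45 just misses (two-sided p = 0.053). The analysis text should therefore say which version applies.
- **A separate SAP may settle sidedness.** It may, but it cannot make 45 follow from the inputs printed beside it.
- **Little harm follows, because power is adequate on every reading.** True for power, which runs from 81% to 92% at 45 per group. It does not answer which error rate governs the primary claim.

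**Conclusion.** The concern holds. For 80% against 50% at 80% power, the stated one-sided 5% level requires 31 per group (37 corrected), not 45. The figure of 45 is reproduced by the two-sided 5% formula with continuity correction, and the total of 100 then follows. As printed, the power is understated for the stated test (92%, or 88% corrected, against 80%), and the primary success threshold has two readings that differ by two responders in 45, about 4 percentage points.

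This rests on the article's own response rates, equal groups and 45 evaluable children per group. That the analysis is two-sided is inferred from the usual form of the chi-square test. The sample size is not too small on either reading. The correction is still necessary, because the stated level contradicts the number it is meant to justify and leaves the error rate of the primary test open.

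**What to change.** In the Sample size calculation section, replace the one-sided 5% level with a two-sided 5% level and name the method: chi-square test with continuity correction. In the Primary outcome part of the Statistical analysis section, write two-sided beside α = 0.05 and say whether the primary chi-square test will use the continuity correction. With the correction, power at 45 per group is 81%; without it, 87%.

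If the sponsor really intended a one-sided 5% test, these changes do not apply. The 45, the 80% power and the analysis text would then have to be restated together, and the one-sided choice justified.

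The recommended change costs a few words in two sections. The 45 per group and the 100 in total stay as they are.

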### Statistical analysis

#### Primary outcome

Outcomes will be analysed according to the ITT analysis. For the primary outcome, the χ^2^ test will be used to compare the proportions of patients with >50% reduction of symptoms of nausea (ie, severity, incidence and frequency of nausea) after 12 months’ follow-up between the two groups (HT vs SMT). For all analysis, the significance level for statistical analysis is set at α=0.05. Multiple imputation will be applied to deal with cases of missing data.

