**Figure 1 F1:**
[figure not shown]
Standard Protocol Items: Recommendations for Interventional Trials figure displaying the trial design and the outcome measurements. After screening for eligibility (T-1), children and parents sign the informed consent form and fill in the baseline questionnaire (T0). Children are then randomised in the hypnotherapy or standard medical treatment group. Assessments take place before the start of treatment (baseline; T0), 6 weeks after the start of treatment (T1), 3 months after the start of treatment (T2), 6 months’ follow-up (T3) and 12 months’ follow-up (T4).

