### Outcomes

#### Primary outcome

The primary outcome of the RCT is the proportion of patients with at least 50% reduction of their symptoms of nausea compare to baseline at 12 months’ follow-up. Children and adolescents report symptoms of nausea at home by using the 7-day diary. To promote retention and complete follow-up, children and parents will be reminded on regular basis, via email and phone calls, to fill in the 7-day diary and other questionnaires.

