##### Seven-day diary

The 7-day diary is used by children and adolescents to score the severity, incidence and frequency of symptoms of nausea, every day during seven consecutive days.^13 21 22^

SON is assessed by the ‘nausea face’ analogue scale, a validated tool in the paediatric population.^23^ Children rate their degree of nausea on a day using six faces: face 0 indicates no nausea, and face 6 indicates nausea as bad as it can be imaged. Scores on the ‘nausea face’ scale are transported to a daily 0–10 score. Face 0, no nausea, is scored as 0, face 1 is scored as 2, face 2 is scored as 4, face 3 is scored as 6, face 4 is scored as 8 and face 5 is scored as 10.^23^ SON score is calculated by summing up the scores of 7 days, giving a maximum score of 70.^13 20–22^

The *incidence* of nausea is assessed using the ‘Nausea Incidence’ Scale (NIS), adapted from the 5-point dyspepsia Likert scale.^24 25^ It measures the incidence of symptoms during a day, where score 0 for no nausea, score 1 for 1–2 times a day, score 2 for 3–5 times a day, score 3 for intermittent symptoms and score 4 for symptoms were always present. The total sum of the scores of 7 days indicates the severity of the nausea during a week, as experienced by the child. The maximum total score is 28.^13 20–22^

The *frequency* of symptoms of nausea is recorded in minutes/hours per day and is scored by children as 0 when there was no nausea, one if children had <10 min of nausea, 2 for 10–30 min of nausea, 3 for 30 min–2 hours of nausea, 4 for 2–4 hours of nausea and 5 if the nausea lasts >4 hours a day. The ‘Nausea Frequency Score’ (NFS) is calculated by summing the scores of the 7 days, with a maximum of 35.^13 21 22^ Treatment success is defined as at least 50% reduction in the SON, NIS and NFS.

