#### Secondary outcomes

For the secondary outcomes, including the potential influence on abdominal pain, dyspeptic symptoms, health-related QoL, anxiety, depression, work absenteeism by parents, school absenteeism by children, somatisation and adequate relief, the Student’s t-test will be used for means of normally distributed data, the Mann-Whitney U test for non-parametric data and the χ^2^ test to compare proportions. To calculate the cost-effectiveness, cost–utility and cost-effectiveness ratios will be calculated for the extra costs per child with >50% reduction of symptoms of nausea and the extra costs per QALY.

As secondary analysis, the proportion of patients with >50% reduction of their nausea (severity, incidence and frequency) after treatment, 6 months’ and 12 months’ follow-up will be compared between groups using multivariate logistic regression correcting for age and centre.

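### The primary χ² test is valid but makes no use of the T0 nausea score that defines response, so precision may be lost; prespecifying adjustment would cost almost nothing

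*Protocol article*

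**What the plan says.** - **Primary test** (Statistical analysis, Primary outcome): the χ² "test will be used to compare the proportions of patients with >50% reduction of symptoms of nausea" between HT and SMT after 12 months. No covariate is named. The level is 0.05 with the number of sides not given, and missing data are to be multiply imputed.
- **Endpoint** (Outcomes, Primary outcome): "at least 50% reduction of their symptoms of nausea compare to baseline at 12 months’ follow-up". The Seven-day diary section adds: "Treatment success is defined as at least 50% reduction in the SON, NIS and NFS". SON is the severity score (maximum 70), NIS the incidence score (28) and NFS the frequency score (35).
- **Baseline** (Figure 1 legend): T0 is assessed before treatment starts.
- **Adjusted analysis** (Statistical analysis, Secondary outcomes): response after treatment, at 6 months and at 12 months is to be "compared between groups using multivariate logistic regression correcting for age and centre". Baseline nausea is not in that model.
- **Allocation** (Randomisation, blinding and treatment allocation): 1:1 in random blocks of 2, 4 and 6. No stratification factor is named.
- **Design assumptions** (Sample size calculation): "we expect that 80% of the children in the HT group will have >50% reduction of their symptoms of nausea after 1 year", against 50% under SMT. This gives 45 per group for 80% power at a one-sided 5% level, and 100 children after 10% dropout.

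**The concern.** Measuring response as a percentage fall from baseline uses the baseline value but does not remove the dependence of response on it. A child who starts high may be more or less likely to halve the score than one who starts low. Regression to the mean can cause this, and the Discussion itself notes that severity of functional symptoms varies over time. The inclusion criteria set no minimum nausea score, and daily SON moves in steps of 2, so halving may mean different things at the two ends of the scale.

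If baseline does predict response, an unadjusted test leaves that predictable part in the error term. In any single trial, a chance difference between the arms in starting nausea also feeds into the estimated difference. The trial is open-label with a self-reported outcome, so a critic could say that one arm began with children whose scores were easier to halve. A prespecified adjusted analysis answers that better than one added afterwards. What is at stake is precision and robustness of the estimate, not the validity of the test.

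**Working it through.** **Inputs.** From Sample size calculation: p₁ = 0.80, p₂ = 0.50, 45 per group, 80% power, 5% level (called one-sided), 10% dropout. From Statistical analysis: α = 0.05, sides not stated. Assumed: r, the correlation between T0 nausea and response, taken from 0 to about 0.46 because the documents give no value.

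**1. The plan's own sample size.** With p̄ = 0.65 and Δ = 0.30, n = [z_α√(2·0.65·0.35) + z_β√(0.80·0.20 + 0.50·0.50)]² / Δ².
- Two-sided: (1.960×0.6745 + 0.842×0.6403)² / 0.09 = 38.5, so 39; with continuity correction, 45.
- One-sided: (1.645×0.6745 + 0.842×0.6403)² / 0.09 = 30.2, so 31; with continuity correction, 37.

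The stated 45 is the two-sided, continuity-corrected figure, and 90/0.9 = 100. The mismatch with the one-sided label is a separate matter; below, two-sided results come first.

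**2. Power of the planned test at 45 per arm (uncorrected).** Power = Φ[(0.30√45 − z_α×0.6745)/0.6403].
- Two-sided: Φ(1.08) = 86%.
- One-sided: Φ(1.41) = 92%.

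**3. What adjustment could add.** 4,000 simulated trials per row, 45 per arm, 80% v 50%, two-sided 5%. The logit of response is linear in a standardised baseline score, with the same slope in both arms. The table compares the χ² test with a logistic likelihood-ratio test adjusted for baseline. The variance ratio is for the standardised risk difference, adjusted over unadjusted.

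| r (control arm) | χ² power | Adjusted power | Variance ratio |
|---|---|---|---|
| 0.00 | 87.0% | 86.9% | 1.01 |
| 0.14 | 87.7% | 87.8% | 0.99 |
| 0.23 | 87.5% | 88.9% | 0.97 |
| 0.35 | 88.0% | 91.2% | 0.89 |
| 0.46 | 86.8% | 92.7% | 0.82 |

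Monte Carlo standard error is about √(0.87×0.13/4000) = 0.5 points. With no treatment effect, both tests rejected in 5.0% to 5.7% of runs.

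A second simulation used the analysis proposed here: a standardised risk difference adjusted for baseline and age. It gave gains of about 0, 2, 4 and 6 points at r of about 0, 0.24, 0.35 and 0.46, variance ratios from 1.03 down to 0.82, and type I error of 4.6% to 5.8%. A ratio of 0.82 is worth 45/0.82 ≈ 55 children per arm.

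**4. One-sided 5%.** With the approximate variance factor 1 − r², power rises from 92% to 93%, 94%, 96% and 97% at r = 0.2, 0.3, 0.4 and 0.5, a gain of about 1 to 5 points.

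**5. Chance imbalance.** The difference in mean baseline between arms has SD √(2/45) = 0.21 baseline SDs, so a gap above 0.3 SD occurs in about 15% of trials. The within-arm SD of response is √[(0.16 + 0.25)/2] = 0.45. A 0.3 SD gap shifts the estimate by r×0.45×0.3, which is about 5 percentage points at r = 0.4 and about 3 at r = 0.2.

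**6. Model size.** Expected non-responders are 45×0.20 + 45×0.50 = 31.5. Treatment, T0 score and age use three coefficients, 10.5 non-responders each. Ten centre indicators would make 13 coefficients, about 2.4 each.

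**The case against.** The strongest reply is that nothing here is wrong. A χ² test of two randomised proportions is valid, fits the way the trial was sized, and exceeds the 80% target at the plan's own rates. Each child is already compared with his or her own baseline, so the remaining link between baseline and response may be weak. The plan also has an adjusted analysis of the same endpoint, with age and centre. All of this stands, and it limits the point to efficiency.

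Three stronger readings are tempting, and the documents support none of them.
- *Chance imbalance biases the primary result.* It does not over repeated trials. It is sampling variation that the test's error rate already covers, as the type I error rates show.
- *Precision is certainly lost, or power would rise by 10 points.* The loss depends on a correlation the documents do not report. A rise from 80% to 90% needs r = 0.5 and a starting power of 80% at a two-sided level. The article states a one-sided level, and the two-sided uncorrected test starts at 86%. One simulation at r of about 0.61 did give 85.9% v 96.6%, but nothing in the documents points to a correlation that high.
- *Baseline nausea is used nowhere in the analysis.* The article does not list the imputation variables, so the T0 score may be among them. What can be said is that it is a covariate in no stated comparison.

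Two further objections concern the remedy. Success depends on SON, NIS and NFS together, so adjusting for SON alone is a choice; it keeps the model small, and what matters is that the covariate is fixed beforehand. Leaving centre out of the primary model also needs a reason, and the sparse cells in step 6 supply it.

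**Conclusion.** The point holds as a recommendation, not as an error or contradiction. The primary analysis and the one adjusted model both leave out the T0 nausea score, a measurement the endpoint cannot be formed without.

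For r from 0 to about 0.46, adjustment is worth roughly 0 to 6 power points (two-sided). If r is zero, the variance penalty is about 1% with baseline alone and at most about 2–3% with age added. Adjustment also takes the effect of chance baseline imbalance out of the estimate.

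These figures rest on the plan's 80% and 50% response rates, 45 analysed children per arm, and a baseline effect that is linear on the logit scale and equal in the two arms. The trial does not need the change to reach its stated power. It is worth making because the likely gain outweighs a negligible cost.

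**What to change.** In Statistical analysis, Primary outcome, prespecify a logistic regression of 12-month treatment success on treatment, T0 SON total (continuous) and age. Report the standardised difference in response proportions, HT minus SMT, with its 95% CI, pooled over the imputed datasets. The target remains the difference in proportions, not a conditional odds ratio. An estimate with a standard error pools directly under multiple imputation, whereas a χ² statistic needs a special combining rule. Keep the unadjusted χ² test as a sensitivity analysis.

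In Statistical analysis, Secondary outcomes, add the T0 nausea score to the model alongside age and centre. Centre can stay in that secondary model only: 11 centres among about 90 to 100 children give roughly 8 or 9 children per centre, split over two arms.

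The cost is wording in the analysis plan and a few lines of code, fixed before outcome data are analysed, with no new data or patients. The one downside is a slightly less simple primary test.
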